### Outcome measures and data collection

The primary outcome measure is the quality of life as reported by the patient or proxy. The EuroQoL-5D (EQ-5D) is a standardized instrument for use as a measure of health outcome. It is among the most commonly used instruments for femoral fracture patients [28, 29]. EQ-5D use is recommended for the assessment of quality of life in trauma patients, especially for economic assessments [30, 31]. The EQ-5D-5 L descriptive system consists of five dimensions of health (mobility, self-care, usual activities, pain/discomfort anxiety/depression), each with five possible answers. It is available in a self-report and a proxy version. The patients’ EQ-5D-5 L health status will be converted into utility scores using the Dutch tariff [32]. Utility scores rang from zero to one, with lower scores indicating poorer quality of life.

The following secondary outcome measures will be used:
**Quality of life, measured with the QUALIDEM;** QUALIDEM (DL010) measures quality of life in persons with dementia (regardless of severity) who live in a nursing home or elderly care facility [33]. The instrument has been developed by the Trimbos Institute and VUmc/EMGO-institute, department of Psychiatry and department of Social and Elderly Care [34]. The QUALIDEM consists of 37 items about the last 7 days rated on a four-point Likert scale. Items are divided into nine subscales (i.e., care relationship, positive affect, negative affect, restless tense behavior, positive self-image, social relations, social isolation, feeling at home, and having something to do). Caregivers complete the questionnaire, which has acceptable psychometric properties [33, 35].**Level of pain and analgesic drug use**: The level of pain will be determined using the Pain Assessment Checklist for Seniors with Limited Ability to Communicate (PACSLAC), which was designed to be a clinically useful scale for assessing pain in patients with dementia [36]. This instrument has been shown to be among the instruments with the strongest psychometric properties for measuring pain and lack of comfort in elderly in a long-term care setting [37]. The instrument is a 24-item questionnaire covering three sub-scales (facial and vocal expression, resistance/defense and social-emotional aspects/mood of the patient). A validated Dutch version (PACSLAC-D) is available [38, 39]. Trained caregivers can use the instrument for scoring the presence of pain. The total score is a summation of the 24 items that are each scored as present (1 point) or absent (0 points). The total score thus ranges from 0 to 24. A score of 4 points or higher indicates pain. In addition to the level of pain we will also register the amount of analgesic medications used. All analgesic medication given will be registered from the patients’ medical files. Opioids will be combined. Opioid use will be defined as daily oral morphine need. Daily narcotic use will be calculated using the equivalence scale for 30 mg/day oral morphine. Calculation of the equivalent morphine dosage allows for comparison between the two treatment groups.**Time to death**: Mortality including (presumed) cause of death will be registered. This will be expressed as mean (or median, as applicable) time to death as well as the rate of mortality within 1 week, 30 days, 3 months, and 6 months.**(Surgical) complications**: This will include general complications that may occur in both groups (e.g*.*, urinary tract infection, pneumonia, pressure sores, delirium, and comorbidity related complications like cardiac arrhythmia, aspiration during intubation, CVA) as well as early post-operative complications (e.g., hematoma, bleeding, blood loss, wound leakage, superficial infection, epidural bleeding due to spinal anesthesia) and late post-operative complications (e.g., deep infection, dislocation, or implant failure, blood loss requiring transfusion < 48 h after surgery). Complications will be categorized for level of severity and treatment necessity according to the Clavien-Dindo classification [40].**Satisfaction of the patient (or proxy) with the chosen treatment**: At the last study visit, the patient (or proxy, as applicable) as well as the patient’s caregiver will be asked to complete an 11-point Numeric Rating Score asking about their satisfaction with the chosen treatment. Herein, 0 = extremely dissatisfied and 10 = extremely satisfied. For patients who have died, their relatives and caregiver will be asked to complete this Numeric Rating Scale. Patients relatives will also be asked to participate in an interview about the **Quality of Dying and Death (QODD)**. This is a 17-item interview-based questionnaire asking about 17 end-of-life priorities. Each item includes a filter question reporting what actually occurred during the final period of the decedent’s life (and how often), followed by a rating of what occurred (using a scale ranging from 0 (‘terrible experience’) to 10 (‘almost perfect experience’) [41, 42].**Satisfaction of the patient’s caregiver with the chosen treatment** (11-point Numeric Rating Score, ranging from zero (extremely dissatisfied) to 10 (extremely satisfied).**Health care resource utilization (with associated costs)**; relevant data will be collected using a questionnaire that is based on the validated Medical Consumption Questionnaire (iMCQ; institute of Medical Technology Assessments iMTA, Erasmus University, Rotterdam. NL) iMCQ details medical specialist care, physical therapy, hospitalization, nursing home, medication use, and other costs directly associated with diagnosis, treatment, and rehabilitation. Health care use and associated costs until 6 months after trauma will be measured in accordance with economic guidelines [43]. Cost prices of the standardized referral strategy will be determined by bottom-up micro-costing method. The incremental cost-utility ratio of nonoperative management versus operative management will be expressed as costs per Quality Adjusted Life Years (QALY) (EQ-5D utility score) gained, with confidence ellipses and acceptability curves. A cost-effectiveness analysis, with QUALIDEM score as outcome measure, will also be done.

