## Background

Proximal femoral fractures are amongst the most common fractures in the elderly [1] with the incidence rate increasing with age. In the Netherlands 20,000 patients are admitted with a proximal femoral fracture to the hospital each year [2, 3]. This number is expected to rise because of our ageing society. Approximately 20% live in a nursing home prior to the fracture. Proximal femoral fractures result in activities of daily living (ADL) dependence and increased morbidity, strongly diminishes the patients’ (health-related) Quality of Life (QoL) and total health care costs [4–7].

A proximal femoral fracture is also strongly associated with mortality. Over 30% of patients die within the first year and 8–13.3% die within the first month [8–10]. Mortality is highest among elderly with both physical and cognitive comorbidities [9, 10]. A 36 and 55% mortality rate within 6 months after fracture has been reported for institutionalized patients and patients with advanced dementia, respectively [11, 12]. This shows that the hip fracture is merely a symptom of the frail status of these patients and the start of cascade breakdown at the end of life.

Operative treatment allows early mobilization, is effective in pain relief, and is believed to prevent secondary complications like pneumonia, urinary tract infection, and pressure sores. However, surgery will not prevent frail patients from developing aforementioned complications. Instead, patients may develop additional surgical complications like bleeding, infection, and non-union, necessitating further (operative) interventions [13]. Hospital admission after a proximal femoral fracture itself can provoke cognitive impairment or delirium in these patients who often live in delicate equipoise in an institutionalized setting.

Although surgery is considered a good analgesic option, it is not the only analgesic option. Moreover, surgery also has disadvantages. It is questionable whether surgery is beneficial in terms of quality of life and whether surgery is satisfactory for family and caretakers involved. The World Health Organization (WHO) definition for palliative care supports a holistic approach in facing life-threatening illness, which is a proximal femoral fracture in a frail elderly patient. Randomized trials comparing operative and nonoperative management in institutionalized elderly are scarce, due to ethical issues, and focus on mortality instead of quality of life.

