### Recruitment and informed consent

Eligible persons presented to the Emergency Department (ED) with a proven proximal femoral fracture will be informed about the study in the ED or upon admission at the surgical or geriatric ward. After an explanation of the study, they will receive written information and a consent form from the attending physician, the clinical investigator, or a research assistant. Patients meeting all inclusion criteria and none of the exclusion criteria will be recruited in the hospital within 48 h after hospital admission. Should patients not be able to sign informed consent themselves, a legal representative (proxy) will receive verbal and written information about the study by the attending physician, the clinical investigator, or a research assistant, and will be asked to consent with participation of the patient. After signing informed consent by patient or proxy, the shared decision process will be carried out using a structured approach. This will result in identifying the primary treatment that is deemed best for the individual patient. Participation in this study is on a voluntary basis. If patients (or proxy on their behalf) do not wish to participate, they can do so without specifying why. Deciding not to participate in the study will not affect regular treatment and follow-up care. Participants are allowed to withdraw from the study at any time after they have given their written consent.

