### Study procedures and follow-up

Patients will be followed until 6 months after trauma or until death, whichever comes first. In addition, at the 6-month follow-up contact, the researcher or research assistant will document any secondary intervention that may be planned for the patient. A schedule of events is shown in Table 1. A flow chart is shown in Fig. 1.

**Table 1 Tab1:** Schedule of events and follow-up

Radiographs & Event forms	Screening	Enrolment	7 days (4–10 days)	14 days (11–17 days)	30 days (23–37 days)	3 months (11–15 weeks)	6 months (6–7 months)
X-ray or CT-scan	X						
Screening	X						
Informed Consent		X					
Shared Decision		X					
Baseline Data			X				
General Clinical FU			X	X	X	X	X
QoL (EQ-5D and QUALIDEM)			X^a^	X	X	X	X
PACSLAC and Analgesic use			X^a^	X	X	X	X
Complications and mortality			X	X	X	X	X
(Secondary) Interventions			X	X	X	X	X
Satisfaction of patient (or proxy)			X^b^	X^b^	X^b^	X^b^	X
QODD			X^b^	X^b^	X^b^	X^b^	X^b^
Satisfaction of caregiver			X^b^	X^b^	X^b^	X^b^	X
Health Care Use			X^a^	X	X	X	X
Early Withdrawal			^c^	^c^	^c^	^c^	^c^

EQ-5D is completed by proxy and (if possible) by patients themselves

^a^Asking for current and pre-trauma status; ^b^Only if patients died prior to that follow-up moment; ^c^Only if applicable

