### Statistical analysis

Data will be analyzed using the Statistical Package for the Social Sciences (SPSS) version 24.0 or higher (SPSS, Chicago, Ill., USA) and will be reported following the STrengthening the Reporting of OBservational studies in Epidemiology (STROBE) guidelines. Normality of continuous data will be tested with the Shapiro-Wilk test. Homogeneity of variances will be tested using the Levene’s test. A two-sided *p*-value < 0.05 will be taken as threshold of statistical significance in all statistical tests. The analysis will be performed on a per-protocol basis, (as that is the most conservative approach) and verified by an intention-to-treat analysis if needed. Patients who have died will remain in the analysis as censored. If necessary, missing values will be replaced using multiple imputation following the predictive mean matching method, using ten imputations.

Descriptive analysis will be performed in order to report the outcome measures and other variables collected for the entire population as well as per treatment group. Continuous data will be reported as mean and SD (if Normal) or median and quartiles (if non-Normal), categorical data as number with percentage.

Univariate comparison between the groups will be done using Student’s T or Mann-Whitney U-test (for Normal and non-Normal data, respectively), or Chi-squared test or Fisher’s Exact test (categorical data, as applicable). The Student’s T-test will be done with equal variance assumed or not assumed, based upon the results of the Levene’s test.

For the primary outcome measure, a non-inferiority margin of 0.15 points for mean EQ-5D scores was chosen because it is reasonable and on the border of what would be considered a clinically important effect. The null hypothesis in the non-inferiority framework is that nonoperative management is inferior to operative management with regards to the EQ-5D score. This hypothesis will be tested through the adjusted contrast between the two interventions at 6 months. Specifically, the 95% confidence interval of the estimated contrast will be examined, and if the limit of the interval is less than the threshold value of 0.15 points, non-inferiority of nonoperative management to operative management at 6 months will be concluded.

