Multivariable analysis for continuous outcome measures that are repeatedly measured over time will be done using generalized estimating equations (GEE) for longitudinal analysis on a per-protocol and intention-to-treat basis to investigate the effect of treatment. In the primary GEE model, the primary outcome variable studied (quality of life on EQ-5D) will be analyzed as a dependent variable, using treatment (nonoperative versus operative) as between subjects variable and time as within subjects variable. The interaction term of group and time (group x time) will be assessed, to evaluate whether the change over time differed between groups. Analyses will be corrected for baseline differences and all models will be corrected for center of inclusion. Repeatedly measured continuous secondary outcome variables will be analyzed using similar GEE models. Continuous outcome measures only ones and dichotomous secondary outcome measures will be analyzed using multivariable linear regression models and logistic regression models, respectively.

Subgroup analysis are planned for patients with an intracapsular or extracapsular fracture.

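### A mean or median time to death is poorly defined when many patients outlive the 6-month follow-up, and no listed method handles censoring

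*Protocol article*

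**What the plan says.** The Protocol article lists time to death among the secondary outcomes and fixes its summary under Outcome measures and data collection: "This will be expressed as mean (or median, as applicable) time to death as well as the rate of mortality within 1 week". The list of times goes on to 30 days, 3 months and 6 months. The outcome is also part of the stated aim of the study.

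Follow-up is finite (Study procedures and follow-up): "Patients will be followed until 6 months after trauma or until death, whichever comes first". It can end earlier (Recruitment and informed consent): "Participants are allowed to withdraw from the study at any time after they have given their written consent".

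Under Statistical analysis, continuous data are described by mean and SD if normal and by median and quartiles if not. Then: "Univariate comparison between the groups will be done using Student’s T or Mann-Whitney U-test", with Chi-squared or Fisher tests for categorical data. Repeated continuous outcomes go to GEE. For the rest: "Continuous outcome measures only ones and dichotomous secondary outcome measures will be analyzed using multivariable linear regression models and logistic regression models, respectively". No Kaplan-Meier, log-rank, Cox or restricted-mean method is mentioned.

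The only sentence on censoring stands in the general paragraph on analysis sets and missing data: "Patients who have died will remain in the analysis as censored".

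**The concern.** For a death endpoint, the death is the event. The censored patients are those alive at 6 months and those who withdraw. The choice between mean and median in the outcome definition mirrors the normality rule of the Statistical analysis section, so the natural reading is an ordinary mean or median compared by t-test or Mann-Whitney. Patients alive at 6 months have no death time to put into such a summary. Either they are left out, and the comparison is made only among those who died, or 6 months is entered as if it were a death time.

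The sentence on censoring adds a risk. It is not restricted to any outcome, and applied literally to time to death it would swap events and censored observations.

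The article itself cites unadjusted pooled odds ratios of 3.95 (30 days) and 3.84 (1 year) for mortality with nonoperative management, and its results are meant to inform guidelines. A report that time to death was similar in the two groups could be taken to mean that survival was similar.

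**Working it through.** The article gives no design figure for time to death, so there is none to reproduce. The check asks how far a mean among decedents can depart from the survival difference.

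**Inputs from the Protocol article**
- 6-month mortality of 36% (institutionalized patients) and 55% (advanced dementia), from Background.
- 30-day mortality of 8–13.3% in hip fracture patients, from Background.
- Unadjusted odds ratios of 3.95 (30 days) and 3.84 (1 year), from Background.
- Planned total of 160 patients, from Sample size calculation.

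**Assumptions made here**
- Horizon T = 182.5 days.
- The mortality figures are used as illustrative group rates; the article does not give rates by group.
- Exponential or Weibull survival, complete follow-up, and 80 patients per group.
- In one scenario the 1-year odds ratio is applied at 6 months.

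**Share without a death time.** 1 − 0.55 = 45% to 1 − 0.36 = 64%.

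**Constant hazard.** With p the 6-month mortality:
- hazard λ = −ln(1 − p)/T
- mean time among decedents m = 1/λ − T(1 − p)/p
- restricted mean survival RMST = p/λ

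For p = 0.36: 1/λ = 182.5/0.4463 = 408.9; m = 408.9 − 182.5 × 0.64/0.36 = 84.5 days; RMST = 0.36 × 408.9 = 147.2 days.

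For p = 0.55: 1/λ = 182.5/0.7985 = 228.5; m = 228.5 − 182.5 × 0.45/0.55 = 79.2 days; RMST = 0.55 × 228.5 = 125.7 days.

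The gap is 5.3 days among decedents and 21.5 days in RMST. The Kaplan-Meier median would be not reached vs 158 days.

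**Other curve shapes.** Weibull curves were passed through assumed 30-day and 6-month mortality:

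| Scenario (mortality, group A vs B) | Decedent mean, days | Gap | RMST, days | Gap | Ratio of gaps |
|---|---|---|---|---|---|
| Constant hazard, 36% vs 55% at 6 months | 84.5 vs 79.2 | 5.3 | 147.2 vs 125.7 | 21.5 | 0.25 |
| Weibull, 13.3% vs 20% at 30 days, 36% vs 55% at 6 months | 63.8 vs 63.3 | 0.5 | 139.8 vs 116.9 | 22.9 | 0.02 |
| Weibull, 13.3% vs 37.7% at 30 days, 36% vs 68% at 6 months (odds ratios 3.95 and 3.84) | 63.8 vs 43.7 | 20.1 | 139.8 vs 87.6 | 52.2 | 0.39 |
| Weibull, 13.3% vs 37.8% at 30 days, 36% vs 55% at 6 months | 63.8 vs 31.1 | 32.7 | 139.8 vs 99.2 | 40.6 | 0.81 |

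**Direction.** In general RMST = T − p(T − m). If both groups have p = 0.55 and their decedent means differ by 20 days, the RMST difference is 0.55 × 20 = 11 days. The decedent mean then overstates.

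**What the fixed-time rates retain.** Simulated power with 80 per group (3000 runs, two-sided 5%):
- Constant hazard, 36% vs 55% (hazard ratio 0.7985/0.4463 = 1.79): t-test among decedents 7%, log-rank 70%, comparison of 6-month proportions 67%. Closed-form power for the last two is 70% (about 73 deaths) and 68%.
- Second table row: 5%, 67% and 67%.
- Third table row: 35%, 99% and 98%.

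**The case against.** The strongest defence is that the same sentence also plans mortality at four fixed times. Categorical tests and logistic regression handle these properly when vital status is known, and at 6 months they lose almost nothing against a log-rank test (67% vs 70%). This stands. A reader might infer that the plan as a whole would show only a fraction of any survival difference. The document does not support that: the shrinkage belongs to a decedent-only mean under assumed group rates, and its direction can reverse.

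A reader might also infer that the article commits to linear regression of time to death, or that it censors deaths in the survival analysis. Neither is stated. The linear-regression rule is general and fits the satisfaction scores without strain. The censoring sentence most naturally concerns the repeated EQ-5D analysis. It is the article's only explicit statement on deaths in the analysis, so deleting it would go too far.

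A decedent-only analysis is not stated either. The permitted median could be a Kaplan-Meier median. If survivors were given 6 months and follow-up were complete, the mean would be the restricted mean under another name. Both are possible readings, but the article says neither, and its general rule for choosing between mean and median points to normality instead.

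Finally, this is a secondary outcome in a condensed article, and a fuller plan may specify survival methods. Absence of those methods alone would not be a finding. What remains is that the article states a summary that cannot be computed as worded for patients who outlive follow-up.

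**Conclusion.** The point holds in a limited form. Read as an ordinary mean or median, the stated summary is either restricted to those who died or treats the end of follow-up as a death, with 45–64% of patients possibly alive at 6 months. In the illustrative constant-hazard case (36% vs 55%), a decedent-only mean shows about 5 of about 21.5 days. Across the four scenarios tabulated it shows between 2% and 81% of the restricted-mean difference, and with equal mortality it overstates. These sizes rest on assumed group rates and curve shapes and on complete follow-up; the number of withdrawals is unknown.

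The fixed-time mortality rates are sound where vital status is complete and would still show a difference. The defect therefore lies in one component of one secondary outcome. It is worth correcting because time to death is part of the study aim and the component is easily misread.

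**What to change.** - Replace the mean or median time to death with Kaplan-Meier curves by treatment group, and add an adjusted Cox model and/or the difference in restricted mean survival to 6 months.
- Define deaths as events. Censor survivors at 6 months and withdrawals at last contact.
- Keep the mortality rates at 1 week, 30 days, 3 months and 6 months.
- Limit the sentence on deceased patients remaining in the analysis as censored, so that it does not apply to time to death.

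The cost is a few lines of wording. Dates of death and follow-up are already part of the planned data, the methods are standard, and neither sample size nor visits change.

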The economic evaluations will be done from a societal perspective. Intervention costs and health care utilization costs until 6 months after inclusion will be measured in accordance with economic guidelines [45]. Cost prices of the standardized referral strategy will be determined by bottom-up micro-costing method. The economic evaluation will be performed in accordance with the intention-to-treat principle. Missing data will be imputed using multiple imputation by changed equations [46]. The Incremental Cost-Effectiveness Ratio (ICER) of nonoperative versus operative management will be calculated by dividing the difference in costs by difference in effects. A cost-utility analysis, with QALY (based on the EQ-5D utility score) as outcome measure, will be done as primary economic analysis. As secondary analysis, a cost-effectiveness analysis, with QUALIDEM as outcome measure, will be done. In order to account for the possible clustering of data, analyses will be performed using linear multilevel analyses [47]. Accounting for the possible clustering of data (e.g., at the hospital level) is very important, as most economic evaluations fail to do so, whereas ignoring the possible clustering of data might lead to inaccurate levels of uncertainty and inaccurate point estimates [47]. Bootstrapping techniques will be used in order to estimate the uncertainty surrounding the cost-effectiveness estimates. Uncertainty will be shown in cost-effectiveness planes and cost-effectiveness acceptability curves, and sensitivity analyses will be performed in order to test the robustness of the study results [48–50].

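### The cost per QUALIDEM point lets death lower the costs but not the effect, so the arm with more deaths can look cheaper without a matching loss

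*Protocol article*

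**What the plan says.** The economic evaluation is described twice in the protocol article.

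- **Effect measure.** Under Outcome measures and data collection, after the cost-utility analysis: "A cost-effectiveness analysis, with QUALIDEM score as outcome measure, will also be done". Under Statistical analysis the same analysis is ranked: "As secondary analysis, a cost-effectiveness analysis, with QUALIDEM as outcome measure, will be done". In both places the effect is the score, not score-weighted time.
- **Ratio.** The ICER "will be calculated by dividing the difference in costs by difference in effects".
- **Costs.** "Health care use and associated costs until 6 months after trauma will be measured in accordance with economic guidelines". The items include residential care: "iMCQ details medical specialist care, physical therapy, hospitalization, nursing home, medication use". Under Study procedures and follow-up, a patient is followed to 6 months or to death, whichever is earlier.
- **Instrument.** "The QUALIDEM consists of 37 items about the last 7 days rated on a four-point Likert scale". Caregivers complete it for people living in a nursing home or elderly care facility. No value for death is given.
- **Deaths and missing values.** The general part of Statistical analysis keeps patients who died as censored. The economic part follows intention to treat and adds: "Missing data will be imputed using multiple imputation by changed equations".
- **Contrast.** The primary economic analysis uses QALYs based on the EQ-5D utility.

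**The concern.** A ratio of costs to effects can be interpreted only if both parts cover the same patients over the same time. Here a patient who dies on day 20 has about 20 days of measured cost, and the other 160 or so days cost nothing. On the effect side those days have no counterpart, because QUALIDEM rates the past week of a living resident and is not multiplied by time lived. Death therefore lowers the numerator and has no defined place in the denominator.

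Differential death is what the Background leads one to expect. It cites 6-month mortality of 36% in institutionalized patients and 55% in advanced dementia, and unadjusted pooled odds ratios for death with nonoperative care of 3.95 at 30 days and 3.84 at 1 year. The secondary analysis could therefore credit nonoperative care with savings that come from shorter survival. The QUALIDEM analysis is announced in the Abstract, and the Discussion intends the results for guideline updates.

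**Working it through.** The plan gives no figure for this ratio, so there is none to reproduce. The check has two parts.

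**1. What each stated rule does with a death**

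| Rule | Costs | QUALIDEM effect | Does death count as lost effect? |
|---|---|---|---|
| Dead censored, nothing imputed | Counted to death | Scores before death only, or none | No |
| Effects imputed after death, costs not | Counted to death | Survivor-like score | No |
| Both imputed after death | Filled in as if alive | Survivor-like score | No. The saving disappears, but the costs are fictitious |
| QALY with utility 0 after death (for contrast) | Counted to death | Lost time lowers QALYs | Yes |

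The first three rows are readings of the text, which does not say which applies. None makes death lower the effect. In the first two, death also lowers the cost.

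**2. Illustrative size**

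Inputs from the Background: 30-day mortality 8-13.3% (hip fracture patients in general), 6-month mortality 36% and 55%, odds ratios 3.95 and 3.84 (unadjusted).

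Assumptions not in the document:
- The cited mortality applies to the operative arm.
- The 1-year odds ratio holds at 6 months.
- The hazard is constant within days 0-30 and within days 30-182.
- A care day costs EUR 100-250.
- An odds ratio of 2 at both times serves as a lower scenario, to allow for confounding.

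Nonoperative risk: q = OR·p/(1 − p + OR·p).
- 30 days: 8% → 0.316/1.236 = 25.6%; 13.3% → 0.525/1.392 = 37.7%.
- 6 months: 36% → 1.382/2.022 = 68.4%; 55% → 2.112/2.562 = 82.4%.

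Mean days alive to day 182, with a the 30-day risk and b the 6-month risk:

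h1 = −ln(1 − a)/30; h2 = −ln[(1 − b)/(1 − a)]/152; days = a/h1 + (b − a)/h2.

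Example, operative arm with a = 0.08 and b = 0.36: h1 = 0.00278, h2 = 0.00239, days = 28.8 + 117.3 = 146.1. Nonoperative arm with a = 0.256 and b = 0.684: h1 = 0.00984, h2 = 0.00563, days = 26.0 + 76.0 = 102.0. The difference is 44.0 days.

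| Operative risk, 30 d / 6 mo | Days, operative | Days, nonoperative | Difference | Difference with OR 2 |
|---|---|---|---|---|
| 8% / 36% | 146.1 | 102.0 | 44.0 | 20.7 |
| 8% / 55% | 128.7 | 85.8 | 42.8 | 21.7 |
| 13.3% / 36% | 141.6 | 92.7 | 49.0 | 23.2 |
| 13.3% / 55% | 124.6 | 77.6 | 47.0 | 23.8 |

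The differences are 43-49 days, or 21-24 days with an odds ratio of 2.

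Cost difference = days × daily cost:
- Cited odds ratios: 42.8 × 100 ≈ EUR 4,300 to 49.0 × 250 ≈ EUR 12,200.
- Odds ratio 2: 20.7 × 100 ≈ EUR 2,100 to 23.8 × 250 ≈ EUR 6,000.

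If QUALIDEM while alive were equal in both arms and accumulated over time, with zero after death, the nonoperative effect would be 77.6/124.6 = 0.62 to 102.0/146.1 = 0.70 of the operative effect (0.81-0.86 with an odds ratio of 2). As a plain score the difference would be 0. Equal scores while alive are an assumption made to isolate the mechanism, not a prediction.

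**The case against.** The strongest reply is that a journal article condenses the full plan. The QUALIDEM summary used, the scope of imputation and the cost rule after death may all be fixed in a document that is not shown. The article does not say that values after death count as missing, nor that effects are imputed while costs stop. Its imputation sentence does not separate the two, and applied to both it would remove the saving. This stands in part: the picture of an early death with a short cost record and a survivor-level score is an inference, not a stated rule. The point does not need it, because the article itself fixes the effect as a score without survival time and divides costs by it. No reading of its rules for deaths or missing data makes death a loss.

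Three stronger readings are tempting and are not supported:
- *Nonoperative care will appear cheaper at equal quality of life.* The QUALIDEM difference among those still alive can move either way through survivor selection, so a zero difference is not a result.
- *No single QUALIDEM score exists.* The article lists nine subscales, but that does not rule out a total, and leaving out scoring detail is normal in an article.
- *The cited odds ratios measure the effect of treatment.* They are unadjusted, and the Discussion itself expects nonoperative patients to be in worse condition. The direction of the cost distortion needs only more deaths in that arm, from any cause; its size is uncertain.

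The harm is also limited. This is the secondary economic analysis, mortality and time to death are reported separately, and sensitivity analyses are planned. A careful reader would see the survival difference beside the ratio, although the ratio would not include it.

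**Conclusion.** The concern holds for the secondary cost-effectiveness analysis only. As written, it relates a cost difference that in practice shrinks with death to an effect that has no place for death, so the arm with more deaths can look cheaper without a matching loss. The primary economic analysis is not affected, because survival time enters the QALY.

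The illustrative amounts, EUR 4,300-12,200 per patient or EUR 2,100-6,000 with an odds ratio of 2, rest on the assumptions listed with the calculation, above all the daily cost and the use of unadjusted odds ratios. They show that the distortion could be large relative to a cost difference of interest; they do not forecast it. The point is worth correcting before analysis but does not touch the trial's primary conclusion.

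**What to change.** In the economic part of Statistical analysis:

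1. State that QUALIDEM and costs are imputed only for time when the patient was alive, and that nothing is imputed after death.
2. Replace the cost-per-QUALIDEM ratio by side-by-side reporting of QUALIDEM while alive, survival and costs, and keep cost per QALY as the only ratio. Align the matching sentences in the Abstract and under Outcome measures and data collection.
3. If a QUALIDEM ratio is kept, use QUALIDEM accumulated over time alive. State the value assigned to death as an assumption and vary it in a sensitivity analysis. Zero on a rescaled score is only one choice: it equates death with the worst living score, and the result would largely repeat the QALY analysis.

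The cost is some wording and a little programming. Visit scores and mortality are already collected. The downside is that one planned secondary ratio is lost, or becomes less favourable to the arm with more deaths.
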